# Use of a novel supplementary food and measures to control inflammation in malnourished pregnant women in Sierra Leone to improve birth outcomes: study protocol for a prospective, randomized, controlled clinical effectiveness trial

**DOI:** 10.1186/s40795-018-0218-y

**Published:** 2018-04-02

**Keywords:** Supplementary foods, Intrauterine growth restriction, Legumes, Low birth weight, Malnutrition, Pregnancy, Stunting, RUSF

## Abstract

**Background:**

The negative synergy between poor nutritional status and infectious diseases is doubly detrimental in pregnancy. In Sierra Leone, maternal malnutrition is amongst the highest in the world, while maternal mortality is high at 1320/100,000 live births and stunting in under-five is 37.9%, ranked 110/132 worldwide. Maternal malnutrition has been associated with preterm birth, small-for-gestational age infants, and poor maternal outcomes. Infants born prematurely or small-for-gestational age experience higher mortality and are at risk for stunting and decreased cognitive performance. Nutritional interventions alone during pregnancy may not be as effective in the setting of increased inflammation from repeated infections. Interventions are needed to improve maternal outcomes and reduce stunting in this population.

**Methods/design:**

This will be a prospective, randomized, controlled clinical effectiveness trial of an improved supplementary food plus anti-infective therapies compared to standard therapy in malnourished pregnant women. Pregnant women will be randomized to receive a low water activity, ready-to-use supplementary food plus five anti-infective interventions or the standard of care which is 3.5 kg corn/ soy blended flour with 350 mL vegetable oil every two weeks. The five anti-infective interventions are 1) insecticide-treated mosquito net at the time of enrollment into the study, 2) sulfadoxine-pyrimethamine given every 4 weeks, beginning at enrollment or at 13 weeks’ gestation, whichever is later, 3)azithromycin at a dose of 1 g given once at enrollment (after first trimester)and again during 28–34 weeks of gestation, 4)single dose 400 mg albendazole given in second trimester, and 5) testing and treatment for bacterial vaginosis at enrollment and again at 28–34 weeks of gestation. Treatment will be provided for the duration of the pregnancy. The primary outcome measure will be birth length. Secondary outcomes in the mothers will include rates of maternal weight gain and increase in mid-upper arm circumference, and time to maternal anthropometric recovery. Secondary outcomes in the infants will include birth weight, birth head circumference, and linear and ponderal growth.

**Discussion:**

Malnutrition remains a major problem in the developing world with lasting maternal and infant consequences. Maternal malnutrition has been associated with intrauterine growth retardation, low birth weight (LBW), pre-term delivery and poor cognitive development. Nutritional interventions alone have not been successful in reducing stunting. By bundling nutritional and anti-infective interventions, we aim to reduce intrauterine growth restriction and low birth weight in moderately malnourished pregnant women in Sierra Leone. If successful, this bundle can easily be implemented by governments or non-governmental organizations.

**Trial registration:**

Clinicaltrials.gov
NCT03079388; Date: March 5, 2017.

## Background

### Maternal malnutrition

Acute malnutrition in pregnancy is a risk factor for adverse outcomes in mothers and their unborn children. There is no universally endorsed method of identification of maternal malnutrition, though a low mid-upper arm circumference (MUAC) has been used reproducibly in a standardized manner [1]. Maternal undernutrition/malnutrition impairs placental formation and results in reduction of placental size, alterations in histomorphology and reduction of blood flow, which can diminish nutrient delivery to the fetus [2]. Maternal malnutrition during pregnancy has been linked to intrauterine growth retardation, low birth weight (LBW), pre-term delivery and poor cognitive development in offspring. Both preterm infants and small-for-gestational-age infants have increased risk of mortality during the neonatal period and extending into early childhood [3]. The long term consequences include limited academic performance, stunted professional achievement, and lower wages as adults [4, 5]. Additionally, undernutrition during pregnancy may result life-threatening hemorrhage, increased risk for sepsis, hypertensive disorders of pregnancy and increased all-cause mortality [6–8]. In Sierra Leone, maternal anemia is amongst the highest in the world with over 50% of pregnant women affected [9]. Maternal mortality is extremely high at 1360/100,000 live births, and stunting in under-five children is 37.9%, ranked 110/132 worldwide [10].

Given the multiple adverse effects of maternal undernutrition, interventions early in pregnancy to improve nutritional status and prevent these outcomes are needed. There have been several trials conducted with aims of improving maternal malnutrition and improving birth outcomes. A large meta-analysis in 2012 including 12 trials demonstrated that pregnant women who received balanced energy and protein supplementation had a significant reduction in stillbirth and risk of small-for-gestational-age infants, as well as, a significant increase in birth weight [11]. Additionally, a second large meta-analysis in 2015 including 15 trials antenatal interventions demonstrated that maternal micronutrient supplementation with iron and folic acid resulted in a significant decrease in the rate of stillbirth, low birthweight infants, and small-for-gestational age infants [12]. Antenatal maternal micronutrient supplementation may, also, result in improved body weight, MUAC, and head circumference persisting into early childhood [13]. Notably, these interventions have not demonstrated any significant effect on birth length or stunting.

In Sierra Leone districts with stunting rates > 40%, the national policy is to provide malnourished pregnant women a daily ration of 250 g corn-soy blend with sugar, 20 ml of oil, 60 mg iron and 400 μg folic acid supplement, from diagnosis until 6 months post-partum; however, coverage and scale-up of this program is limited and has only reached select districts.

### Maternal anemia

Anemia is highly prevalent in women in Sierra Leone at 45% in women of child bearing age. The highest prevalence of 50% is found among women age 15–19 [9]. Anemia during pregnancy may be attributed to poor dietary intake, inadequate absorption and blood loss from intestinal helminths or malaria [14]. The WHO recommends daily oral iron supplementation of 30-60 mg of elemental iron as part of routine antenatal care to reduce the risk of maternal anemia and low birth weight infants [15].

In addition to iron supplementation, preventative treatment of helminth infections has been shown as successful intervention during pregnancy [16–18]. Deworming with albendazole is safe, treats common helminth infections and has been shown to reduce anemia in pregnancy, especially when added to iron supplementation [18]. Additionally, preventing helminth infections is important as infections during pregnancy have been associated with lower cognitive and gross motor functioning in offspring [19]. Deworming of pregnant women should be delivered during antenatal visits; however, only 36% of pregnant women in Sierra Leone are dewormed [9].

### Inflammation during pregnancy

A recent trial in rural Malawi of a lipid-based nutritional supplement for pregnant women and its effect on newborn size did not demonstrate statistically significant difference between groups in the incidence of low birthweight, small-for-gestational age, preterm birth, or newborn stunting [20]. This may be because nutritional interventions for malnutrition may be less effective under conditions with excessive inflammation and infection, and especially so during pregnancy. Undernutrition impairs immune function, prolonging the inflammatory process, which subsequently depletes nutrient supply; therefore, without specifically addressing treatment for infections, undernourished mothers may be less responsive to nutritional interventions. The increased nutrient demands during pregnancy result in a heightened risk for malnutrition and infections for both mother and fetus. Women in Sierra Leone are subject to continuous malaria transmission, as well as poor sanitation and hygiene, with only 5% having access to piped water and 38% having access to improved sanitation [9].

Common infections in Sierra Leone and sub-Saharan Africa include malaria, sexually transmitted diseases and gastrointestinal parasite infestation. Pregnancy is a time when the immune system is less able to recognize and respond to infections, in part because greater immuno-tolerance is needed for a successful pregnancy. The placenta is an organ within which the immune response is blunted [21, 22].

Malaria is the most common cause of illness and death in Sierra Leone [9]. Malaria due to *Plasmodium falciparum*, in particular, is known to be especially damaging in pregnancy due to its high tropism for the placenta, leading to high rates of stillbirth, IUGR, and premature delivery [23, 24]. Ensuring that all pregnant women receive insecticide-treated nets (ITN) as early in pregnancy as possible is also an important component of keeping pregnant women safe from malaria [25]. The World Health Organization recommends the Intermittent Preventive Treatment of malaria during pregnancy (IPTp) which requires that all women residing in malaria endemic regions receive monthly doses of malaria chemoprophylaxis with sulfadoxine-pyrimethamine (SP) during the second and third trimesters of pregnancy [26]. This recommendation for monthly chemoprophylaxis supersedes the prior recommendation of two doses during pregnancy, as it has been shown to be safe and superior in reducing the risk of adverse pregnancy outcomes, even in areas where in vitro SP resistance is widespread [27, 28]. In Sierra Leone IPTp and the distribution of ITNs coverage for pregnant women needs strengthening with only about 41% of women following recommendation [9].

The most recent demographic health survey in Sierra Leone revealed that among women of reproductive age, 22.7% reported having an STI, genital discharge, and/or a genital sore/ulcer, and 26% did not get any treatment [9]. Azithromycin is a safe, broad spectrum antibiotic with activity against several common sexually transmitted diseases including chlamydia, gonorrhea, and chancroid, in addition to having some antimalarial activity. Given twice during pregnancy, azithromycin has been shown to reduce stunting and premature delivery in Malawi [29].

Among the sexually transmitted diseases, bacterial vaginosis has been associated with preterm labor and other adverse pregnancy outcomes. One large study has demonstrated that screening and treatment for bacterial vaginosis significantly reduces rates of late miscarriages [30]. Treatment of symptomatic pregnant woman is widely recommended. Routine screening and treatment of asymptomatic pregnant women remains controversial as a 2013 Cochrane review demonstrated no significant reduction in the odds of preterm birth in women receiving treatment [31]. This may not apply to malnourished women who have ongoing inflammation and an increased risk for preterm birth as there is evidence to support routine testing and treatment of both symptomatic and asymptomatic women in populations at high risk for preterm delivery [32, 33].

## Methods/design

### Study goals

In this study, we aim to determine whether a combined intervention of a specialized nutritious food for pregnant women and a package of anti-inflammatory interventions results in improved birth anthropometry compared with the standard of care.

### Study design

This will be a prospective, randomized, controlled clinical effectiveness trial in pregnant women with malnutrition comparing the impact of combined nutrition and infection control interventions with the standard of care in Sierra Leone. The study will enroll pregnant women at less than 35 weeks of gestation with moderate or severe malnutrition. A probable patient diagram is shown in Fig. 1.

**Fig. 1 Fig1:**
[figure not shown]
Patient flow diagram for clinical trial. *Women 16 years of age or older will be enrolled and followed until 6 months post-partum. **Women less than 35 weeks of gestation will be enrolled

### Study location

The study will enroll patients at twenty antenatal clinics in rural Pujehun District in southern Sierra Leone and 10 antenatal clinics in the Rural Western Area District. In 2013, Pujehun District had the highest rate of under 5 stunting at 46.4% which is 8.4% above the national rate. Mothers who are thin (BMI < 18 kg/m^2^) are more likely to have children that are stunted, identifying Pujehun as an ideal district for a maternal nutrition intervention. The population predominantly belongs to the Mende ethnic group. Plantation farming is a major economic activity in the region with agricultural production of palm oil, cassava, and sweet potatoes [34]. Pujehun is one of the country’s poorest and least developed districts.

### Ethical considerations

We aim to complete the study using the highest ethical standards for clinical trials research in accordance with the Declaration of Helsinki [35]. Ethical approval has been obtained from the Sierra Leone Ethics and Scientific Review Committee (SLESRC) and from the Human Research Protection Office at Washington University in St. Louis. Support has also been obtained from Pujehun District Health Officer. Each subject will be briefed on the study procedures and interventions. Women older than 16 years of age will be eligible to consent for themselves. If a woman younger than the age of 16 desires to participate, consent will be obtained from the parent or guardian. Both verbal and written informed consent will be obtained from all enrollees. Those who are unable to sign or write their names will be asked to document consent using thumbprints.

### Eligibility criteria

Pregnant women presenting to any of the thirty selected antenatal clinics will be screened for enrolment eligibility. Women who have a fundal height no greater than 35 cm, MUAC ≤23 cm, and planning to reside in the study area and attend the antenatal clinic will be considered eligible. MUAC is a reproducible, reliable measure in the field and easily understandable by both health workers and participants. Fundal height will be used as a measure of gestational age. Exclusion criteria will include pregnant women less than 16 years of age who do not have an adult community member willing to consent for them or known complications of pregnancy such as gestational diabetes, pre-eclampsia, hypertension, or severe anemia.

### Outcome measures

The primary outcome measure of interest will be birth length in centimeters. The secondary outcome measures of interests include the total and average weekly maternal weight gain, recovery from maternal malnutrition identified as a MUAC > 23, newborn head circumference, birth weight, infant linear and ponderal growth, and infant survival at 3 months and 6 months.

### Sample size

The sample size will be 1514 pregnant women with malnutrition, divided equally between RUSF and control groups. This sample size allows for a 20% drop out rate and/or exclusion rate due to fundal height, leaving a final sample size of 1200 (600 per group) with a two tailed significance of 0.05, power of 80%. This will allow for detection of a difference of 0.22 SD or 0.5 cm in birth length and a difference of 0.19 SD or 80 g in birth weight.

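### The sample-size figures do not agree: 600 per group gives about 97% power for 0.22 SD and 91% for 0.19 SD, not the stated 80%, though the error is conservative

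*Protocol article*

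**What the plan says.** All the design figures are in the Sample size section. Enrolment is set first: "The sample size will be 1514 pregnant women with malnutrition", "divided equally between RUSF and control groups". An allowance follows: "This sample size allows for a 20% drop out rate and/or exclusion rate due to fundal height". The evaluable number, significance level and power come next: "leaving a final sample size of 1200 (600 per group) with a two tailed significance of 0.05, power of 80" per cent. The section then says that this permits detection of "a difference of 0.22 SD or 0.5 cm in birth length and a difference of 0.19 SD or 80 g" in birth weight.

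The Statistical analysis section names Student's t-test for both birth length and birth weight. The Randomization and blinding section describes allocation of individual participants. The Sample size section mentions no design effect, multiplicity correction or covariate adjustment, and gives no separate sample size for each outcome.

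Fundal height also appears under Eligibility criteria, as a condition of entry: "Women who have a fundal height no greater than 35 cm".

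**The concern.** For a two-group t-test with equal groups, the sample size, significance level and power together fix a single detectable difference in SD units. The outcome's own scale enters only when that difference is converted to centimetres or grams. A paragraph that gives 0.22 SD for one outcome and 0.19 SD for another, from the same three inputs, must therefore contain a wrong figure or omit an adjustment.

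What is at stake is how the result will be read. The paragraph is the benchmark for what the trial could and could not have found in its primary outcome. As it stands, 0.5 cm looks like the smallest birth-length difference the trial has 80% power to find. If the SD-scale figures are right, that difference is smaller. If they are wrong, the SDs behind 0.5 cm and 80 g differ from those the paragraph implies. A reader cannot tell which.

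**Working it through.** **Inputs, all from the Sample size section unless noted.** Evaluable n = 600 per group; allocation 1:1; two-sided alpha = 0.05 (z = 1.960); power = 80% (z = 0.842); differences 0.22 SD (0.5 cm) and 0.19 SD (80 g); two-sample t-test (Statistical analysis section).

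**Step 1. The loss allowance.** 1200 / (1 − 0.20) = 1500, against 1514 stated. Conversely, 1 − 1200/1514 = 20.7%. This step reproduces to within rounding.

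**Step 2. The stated power.** Power ≈ Φ(d × √(n/2) − 1.960), with √(600/2) = 17.32.
- Length: 0.22 × 17.32 = 3.81; 3.81 − 1.96 = 1.85; power = 96.8%.
- Weight: 0.19 × 17.32 = 3.29; 3.29 − 1.96 = 1.33; power = 90.8%.

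The exact noncentral t gives the same values to one decimal. The stated 80% does not reproduce for either outcome.

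**Step 3. Detectable difference at 80% power.** (1.960 + 0.842) × √(2/600) = 2.802 × 0.0577 = 0.162 SD, for any continuous outcome.

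**Step 4. Sample size for 80% power at the stated differences.** n per group = 2 × (2.802/d)². This gives 324.3, so 325, for 0.22 SD, and 434.8, so 435, for 0.19 SD. Neither is 600.

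**Step 5. Possible explanations.**

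| Variant | 0.22 SD | 0.19 SD |
|---|---|---|
| Rounding of the SD figures (0.215–0.225; 0.185–0.195) | 96.1–97.4% | 89.3–92.2% |
| One-sided alpha 0.05 | 98.5% | 95.0% |
| Alpha 0.025 (Bonferroni, two outcomes) | 94.2% | 85.3% |
| Alpha 0.01 | 89.2% | 76.3% |
| Alpha 0.005 | 84.2% | 68.6% |
| 757 per group (no loss) | 99.0% | 95.9% |
| 300 per group (600 read as the total) | 76.9% | 64.3% |

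No row gives 80% for both outcomes. Raising the power instead, the detectable difference at 600 per group is 0.187 SD at 90% and 0.208 SD at 95%. So 0.19 SD would fit a 90% calculation, but 0.22 SD fits none of these. A design effect would have to be 600/324.3 = 1.85 for length and 600/434.8 = 1.38 for weight; none is stated.

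**Step 6. In physical units, if the SD-scale differences are right.** The article states no SDs. Those it implies are 0.5/0.22 = 2.27 cm and 80/0.19 = 421 g. At 80% power the detectable differences are then 0.1617 × 2.27 = 0.37 cm and 0.1617 × 421 = 68 g.

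The stated figures are rounded. If 0.5 cm stands for 0.45–0.55 and 0.22 for 0.215–0.225, the length SD lies between 0.45/0.225 = 2.00 and 0.55/0.215 = 2.56 cm. The detectable difference is then 0.32 to 0.41 cm.

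**Step 7. In physical units, if instead 0.5 cm, 80 g and 80% power are right.** The SDs would have to be 0.5/0.1617 = 3.09 cm and 80/0.1617 = 495 g, and the 0.22 and 0.19 SD figures would be the mistakes. The article does not decide between this and Step 6.

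**The case against.** The strongest reply is that the sentence is literally true if detection is read as detection with at least 80% power, since the trial exceeds 80% for both differences. That stands as far as it goes: the trial is not underpowered for what it names. It does not make 80% the power at 0.22 or 0.19 SD, and it does not explain two different standardised differences.

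A second reply is that a journal article condenses a fuller protocol, where a design effect or another adjustment may be recorded. With outcome-specific design effects the figures could be made to agree. This also stands in part. It means one cannot say that the power is the wrong figure, only that the published figures do not agree and the adjustment, if any, needs stating.

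Three stronger readings are tempting, and the document does not support them.
- A reader might infer that significance could be reached at about half the 0.5 cm target, because 1.96 × 2.27 × √(2/600) ≈ 0.26 cm. That compares a significance threshold with a detectable difference. In a trial with exactly 80% power the threshold is already 1.960/2.802 = 70% of the target, here 0.35 cm. The fair comparison is 0.26 with 0.35 cm.
- A reader might infer that the trial enrols more women than it needs. That would follow only if the SD-scale differences are right and nothing was adjusted, which the article does not establish.
- A reader might infer that randomised women will be removed from analysis for fundal height, because the 20% allowance mentions it after the 1514 have been divided. The Eligibility criteria section and the Subject participation and data collection section apply the criteria before enrolment, and no section drops randomised women from analysis. The wording is loose, no more.

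**Conclusion.** The point holds as an internal inconsistency in one paragraph about the primary outcome. With 600 per group, two-sided alpha 0.05 and the planned t-test, power is about 97% and 91% where 80% is stated, and 80% power corresponds to 0.16 SD for both outcomes. This rests on an unadjusted comparison with the same effective sample size for both outcomes, which is all the article describes. The values in centimetres and grams rest further on SDs back-calculated from rounded figures, so they are approximate.

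The direction is conservative. No test, endpoint or enrolment number is put in doubt, and the document does not show which input is at fault. It is a reporting correction that should be made; it does not threaten the trial's validity.

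**What to change.** Rewrite the Sample size paragraph so that its figures agree:

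- State the SDs assumed for birth length and birth weight, and their source.
- State any design effect, multiplicity correction or other adjustment used, or say that there was none.
- Give the power for each outcome separately at 600 per group. If the SD-scale differences stand and nothing was adjusted, that is about 97% for 0.5 cm and 91% for 80 g, with the differences detectable at 80% power given alongside. If other SDs or an adjustment were used, recompute from those.
- Clarify that the 20% allowance covers loss of the birth measurement, since fundal height is already an entry criterion.

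The cost is one reworded paragraph. Enrolment, outcomes and analysis methods stay as they are.

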### Randomization and blinding

Subjects will be randomized to receive the RUSF or the standard of care (supercereal, oil, and iron and folic acid tablets), using a random number generator which prospectively assigns participants to a study group. Since RUSF is visually distinct from flour, neither the study subjects nor the research study team members working directly with participants will be blinded. Study managers will be blinded to treatment during data analysis.

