### Subject participation and data collection

A study team member will attend each participating antenatal clinic for subject recruitment. All women attending the antenatal clinic will be briefly informed of the study and entry criteria in a group setting. Women willing to be measured and potentially participate will be offered measurement of MUAC and screened for study eligibility.

All women meeting eligibility criteria will be offered enrollment and agree via informed consent. Informed consent will be obtained by the on-site study coordinator. All participants who are 16 years of age or older will be able to consent for themselves as adults. If a participant who is younger than 16 wants to participate in the study, they will be required to have consent from a parent or guardian. Upon enrollment, the participant will be interviewed. Demographic information will be recorded, as well as, time of last menses, estimated date of delivery, and fundal height. Anthropometry will include current weight, height, MUAC, and weight history if available. Available medical records of the women will be reviewed with attention to any current or previous pregnancy complications and medications. Subjects will answer a standard clinical symptoms questionnaire, a food frequency questionnaire, and a Household Food Insecurity Access Scale (HFIAS).

Participants will return for follow-up every 2 weeks for measurements and provision of food until delivery. Since birth measurements are primary outcomes, a birth weight team will be identified and trained in order to obtain accurate birth measurements within 48 h of delivery.

Participation in the study will continue throughout pregnancy, and follow-up with the mother and infant will continue until 6 months postpartum. Mothers and infants will be followed at usual infant clinic follow-up at 6 weeks, 3 months, and 6 months post-partum contact point clinic. Infant weight, linear growth, and morbidity will be monitored. Maternal weight, MUAC and morbidity will be assessed at these visits, as well.

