One limitation of the study is the lack of blinding of the nutritional and anti-infective interventions between the two groups. The study RUSF and standard of care flour are distinctly different in packaging and appearance. Those participants randomized to the intervention group will receive more obvious anti-infective interventions during antenatal visits. Mitigating the un-blinded nature of the intervention distribution is that choice of primary outcome, birth length, will be obtained in a standardized, objective manner. In order to account for this lack of blinding, study managers will be blinded to treatment during data analysis. Another limitation is the possibility that participants will share or trade their assigned food. Participants will be educated about the need to comply with the assigned intervention. We anticipate this will be an unlikely occurrence as past research by our group of compliance with supplementary foods in Malawi rarely demonstrated sharing or trading of assigned foods [44]. An additional limitation of our data will be that the control group will be receiving the standard of care for Sierra Leone, but these interventions are not universally adopted, especially in very rural areas such as Pujehun. This may result in improved outcomes in the control group than would be expected from currently available data for pregnant women and infants.

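### Masking of the birth-measurement team is not provided for, and blinding at the analysis stage cannot make up for that in the primary outcome, birth length

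*Protocol article*

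**What the plan says.** The primary outcome is fixed under Outcome measures: "The primary outcome measure of interest will be birth length in centimeters".

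Randomization and blinding explains that the two foods look different and concludes that "neither the study subjects nor the research study team members working directly with participants will be blinded". The only people it blinds are the study managers, and only while the data are analysed.

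Subject participation and data collection gives the birth measurements to a dedicated group: "a birth weight team will be identified and trained in order to obtain accurate birth measurements within 48 h of delivery". It does not say whether this group knows the allocation. The same section places food provision at the two-weekly visits before delivery.

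The Discussion lists the lack of blinding as a limitation and offers two mitigations. The first is that the "choice of primary outcome, birth length, will be obtained in a standardized, objective manner". The second is: "In order to account for this lack of blinding, study managers will be blinded to treatment during data analysis".

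Sample size sets the scale on which bias has to be judged: "detection of a difference of 0.22 SD or 0.5 cm in birth length and a difference of 0.19 SD or 80 g in birth weight", with 600 per group after losses.

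**The concern.** Measuring a participant's newborn is direct work with participants. With no exception stated, the blinding rule on its ordinary reading takes in the people who record the primary outcome.

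Newborn length is read by hand, and the reading depends on how the infant is positioned and straightened. An examiner who expects one arm to do better can read slightly longer in that arm without intending to. If this happens on average across the trial, it adds a constant to the difference between arms. The t-test cannot tell that constant from a treatment effect, and a larger sample does not reduce it.

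The reason given for open treatment is the appearance of the food. That explains why mothers and food distributors know the arm. It does not explain why a separate team that first sees the infant after delivery has to know it.

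**Working it through.** **Inputs from Sample size:** target 0.5 cm = 0.22 SD; 600 per group; two-sided alpha 0.05; power 80%. **Assumed, because the documents give no examiner-bias figure:** a net mean reading shift *b* between arms of 0.05 to 0.20 cm.

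**1. The plan's own figure.** Implied SD = 0.5 / 0.22 = 2.27 cm. For 80% power to detect 0.22 SD:

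n per group = 2 × (1.96 + 0.842)² / 0.22² ≈ 325

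The stated 600 does not reproduce at 80% power. With 600 per group, 0.22 / √(2/600) = 3.81, and power = Φ(3.81 − 1.96) ≈ 96.8%. This is a separate matter. It does not weaken the present point, since extra subjects reduce random error and not bias. The SD and the 600 are used below as stated.

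**2. Precision of the comparison.**

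SE = 2.27 × √(2/600) = 0.131 cm

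Smallest observed difference that reaches significance = 1.96 × 0.131 ≈ 0.26 cm

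**3. False-positive rate under a reading shift, with no true effect.**

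P = Φ(−1.96 + b/SE) + Φ(−1.96 − b/SE)

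| Assumed shift b | Share of the 0.5 cm target | b/SE | Two-sided false-positive rate |
|---|---|---|---|
| 0 | 0% | 0 | 5.0% |
| 0.05 cm | 10% | 0.38 | 6.7% |
| 0.10 cm | 20% | 0.76 | 11.9% |
| 0.15 cm | 30% | 1.14 | 20.8% |
| 0.20 cm | 40% | 1.52 | 33.2% |

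**4. Sensitivity to the SD.** For an SD between 2.0 and 2.5 cm, the rate is 10.7% to 13.9% at 0.10 cm and 28.3% to 41.0% at 0.20 cm.

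**5. Which safeguards act on b.** The shift enters when the length is read.

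- Training and standardized technique act at that moment. They reduce random error and error common to both arms. They do not by themselves stop a reading from depending on the arm.
- Sealing the database before the code is broken (Data management and analysis) and blinding the managers both act later. They prevent arm-driven choices in cleaning and analysis. They leave b, and every rate in the table, unchanged.

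**The case against.** The strongest reply is that nothing in the article names the birth team as unblinded. The stated reason concerns staff who see the food, the team is described separately, and a condensed article may leave form layout and rostering to a fuller protocol. This stands in part. A reader might infer that the team is definitely unblinded, but the documents support only that no exception is made for it. The point is still more than missing detail, because the article does say who is blinded, who is not, and what is meant to compensate. The last of these is wrong as reasoning.

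A reader might also infer that analysis-stage blinding is the only safeguard. It is not. The Discussion first relies on standardized measurement, the data-collection section adds a trained team and a 48-hour window, and the limitation is openly disclosed.

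A third tempting reading is that the trial is so large that a shift of a millimetre or two would be declared significant. The numbers do not support this. Such a shift lies below the 0.26 cm needed. At 0.10 to 0.20 cm, about 88% to 67% of null trials would still be non-significant, and at 0.05 cm the error rate barely moves. The shifts are assumptions about a net directional bias averaged over 1200 infants, not about error in a single reading.

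**Conclusion.** The point holds in a limited form. As written, the plan allows the primary outcome to be measured by examiners who know the arm, and its claim that blinding managers during analysis accounts for this is incorrect.

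The possible damage runs from negligible (6.7% at 0.05 cm) to serious (33.2% at 0.20 cm). This rests on three things: an assumed net shift, the SD of 2.27 cm implied by Sample size, and 600 infants measured per group. The documents do not show that any such shift exists, and they do not establish that the team in fact knows the allocation. A cheap safeguard is available within the planned structure, so the change should be made. If the team is already masked, the text should be corrected to say so.

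**What to change.** - In Randomization and blinding and in Subject participation and data collection, state that the planned birth team is masked to arm as far as feasible.
- Keep the allocation off the birth forms and any cards the team sees. Where rostering allows, do not assign its members to food or drug distribution. Ask mothers not to disclose which food they received.
- Record for each birth whether the team learned the arm.
- In the Discussion, delete the claim that analysis-stage blinding accounts for open treatment. Describe that step only as protection against arm-driven choices in the analysis.

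**Cost.** Form layout, a short instruction to mothers and some rostering. No additional assessor is called for, but the documents do not give the team's size. With thirty clinics in two districts and a 48-hour window, full separation from distribution may not always be possible. Masking will fail when mothers disclose, which is why unmasking should be recorded. Trial status reports recruitment since March 2017 and still open, so the change would apply only to later births.
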